### Participant withdrawal

Patients will be withdrawn from the study if they (1) withdraw their informed consent; (2) request to withdraw from the trial; or (3) decline to continue treatment or follow up. All source data and source files related to all withdrawn participants will be retained. The time and cause of withdrawal will be recorded on the case report form in detail.

### Monitoring

Progression of the trial, adverse events, and data quality will be monitored by an Independent Data (and safety) Monitoring Board (IDMB), which is independent of the trial Sponsor. The IDMB will be responsible for reporting the security data in the trial to the primary investigator. The primary investigator will submit a list of all suspected SAEs to the Independent Ethics Committee (IEC), as well as a summary of all reported SAEs every 6 months.

### Audits

An inspector will review the incoming data monthly and generate a data query if necessary. The inspector will review whether each electronic case report form is completed accurately. All discrepancies in the electronic case report form will be corrected by the investigator or authorized personnel in an appropriate manner.

### Data management

Data entry and management are the responsibility of an independent data administrator, who will use the EpiData 3.1 software (The EpiData Association, Denmark, Europe). All data will be independently inputted and proofread by two data administrators, to ensure accuracy. The data administrators will list the questions in the case report form in the data request queue (DRQ), and the investigator will respond as soon as possible. The data administrators will then modify, confirm, and enter the data according to the investigator’s responses. Another DRQ can be submitted if necessary. All original files will be kept in accordance with the principles of Chinese Good Clinical Practice, and clinical data will be kept by the investigators for 5 years (starting from the end of the clinical trial). All clinical data pertaining to the trial will be the property of the Sponsor, and the investigators will have no right to disclose these data to a third party without written approval by the Sponsor.

### Sample size

The survival time of the patients will be compared between the two groups by the log-rank test, using PASS Sample Size Software 11.0 (NCSS LLC, Kaysville, Utah, USA) [35]. Based on previous experience [36] and pilot study results, the mPFS was estimated to be 4.1 months in the vinorelbine monotherapy group and 6.7 months in the vinorelbine plus apatinib group (hazard ratio (HR) = 0.61). The recruitment time is expected to be 26 months (from the beginning of recruitment to the enrollment of the last patient) and a 15-month follow-up time is planned. Assuming a dropout rate of 10% across both groups, power of 80%, and two-sided significance of α = 0.05, a sample size of 238 patients (119 in each intervention group) will be required.

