## Discussion

The anti-tumor effect of conventional chemotherapy relies on a single maximum tolerated dose. Despite its wide use, traditional scheduling of chemotherapy cycles is not convenient for patients, as frequent hospital visits for infusion and in-patient admission are required. To reduce the side effects of chemotherapy, treatment cycles are separated by longer intervals. This prospective randomized controlled trial, conducted in Liaoning Province of Northeast China, will be the first to analyze the efficacy of apatinib-targeted therapy, combined with vinorelbine chemotherapy, in treating patients with recurrent or metastatic TNBC, who have previously received anthracyclines and taxanes. Some limitations should be acknowledged in the current study protocol. As all subjects are limited to the northern Chinese population, the study results may not be generalizable to other patient populations. Furthermore, the sample size is relatively small, and this is due to limitations in staffing and funding.

Based on the data from this trial, we hope to identify an optimal treatment regimen that is suitable for female patients with TNBC in Northeast China, who have been treated with anthracyclines and taxanes.

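### The 238 patients for 80% power reproduce only if the 10% dropout is applied per month; with 10% dropout overall the stated inputs need about 152 to 158, and 238 gives about 93-94% power.

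*Protocol article*

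**What the plan says.** The Sample size section of the protocol article states that survival time will be "compared between the two groups by the log-rank test, using PASS Sample Size Software 11.0". For the effect, "the mPFS was estimated to be 4.1 months in the vinorelbine monotherapy group and 6.7 months in the vinorelbine plus apatinib group", with "hazard ratio (HR) = 0.61". For the schedule, "The recruitment time is expected to be 26 months" and "a 15-month follow-up time is planned". The remaining inputs are "Assuming a dropout rate of 10% across both groups, power of 80%, and two-sided significance of" 0.05, and the result is 238 patients, 119 per arm.

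The section gives no time unit for the dropout rate and no number of PFS events. The Statistical analysis section rules out an interim analysis, so no alpha spending enlarges the sample. The Trial status section gives a calendar of its own: recruitment from June 2019 to August 2022, with the primary analysis completed in December 2022.

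**The concern.** With control and experimental medians of 4.1 and 6.7 months and at least 15 months of follow-up for everyone, nearly all patients should have a PFS event. The sample size should then lie only modestly above the number of events, with a further tenth or so for dropout. The stated 238 is well above that.

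The stakes depend on which input is off. If 10% is the overall loss, the trial enrols about 80 patients more than its stated power requires, and readers and the ethics committee are given a power figure that is too low. If 10% per month was meant, the paragraph conceals an assumption that nearly half the patients leave before progression. The Statistical analysis section imputes missing primary endpoint data conservatively, and that imputation would then carry much of the primary result. Without an event target, nobody can tell which of the two designs is intended.

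**Working it through.** **Inputs (Sample size section).** Medians 4.1 and 6.7 months; recruitment R = 26 months; follow-up F = 15 months; two-sided 0.05; power 80%; dropout 10%; N = 238, allocated 1:1. Assumed here: exponential PFS, uniform recruitment, and the 15 months counted from the last enrolment, so T = 41 months.

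**Hazards.** ln 2/4.1 = 0.1691 and ln 2/6.7 = 0.1035 per month. The ratio is 4.1/6.7 = 0.612, in agreement with the stated 0.61.

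**Reproducing 238.** Take 10% per month as a competing loss hazard in each arm, η = −ln 0.9 = 0.1054 per month. With s = λ + η, the probability of an observed event is (λ/s) × {1 − [exp(−sF) − exp(−sT)]/(sR)}.
- Control 0.615, experimental 0.491, mean 0.553.
- Replacing λ/s by η/s gives the proportion lost before an event: 0.383 and 0.501, mean 0.44.
- Expected events: 238 × 0.553 = about 132.
- A Lakatos-type log-rank calculation gives N = 237.7, that is 119 per arm, with power 80.0%. The two simple event formulas below bracket it: 130.2/0.553 = 235 and 135.4/0.553 = 245. A log-rank simulation of 238 patients gave about 78% power.

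So N and power agree with each other if the rate is monthly.

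**The ordinary reading: 10% lost overall.**
1. Events for 80% power, with (1.960 + 0.842)² = 7.849:
   - Schoenfeld: 4 × 7.849/(ln 0.612)² = 130.2
   - Freedman: 7.849 × [(1 + 0.612)/(1 − 0.612)]² = 135.4
2. Event probability without dropout, 1 − [exp(−λF) − exp(−λT)]/(λR): control 0.982, experimental 0.927, mean 0.954.
3. Patients before dropout: 130.2/0.954 = 136.4 to 135.4/0.954 = 141.9. Lakatos-type: 139.0.
4. After dividing by 0.9: 151.5 to 157.7, so 152 to 158. Lakatos-type: 154.5. With the rounded HR of 0.61 the range is 150 to 156.
5. Excess of 238: 238/158 = 1.51 to 238/152 = 1.57, that is 51% to 57% more.
6. Power of 238: events = 238 × 0.9 × 0.954 = 204.
   - Schoenfeld: Φ(√204 × 0.491/2 − 1.960) = 94.0%
   - Freedman: Φ(√204 × 0.388/1.612 − 1.960) = 93.1%
   - Simulation: 93.7%

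**Other readings that do not give 238.**
- Dropout as a hazard of 10% per year: event probability 0.936 and 0.866, mean 0.901; N = 130.2/0.901 = 144 to 135.4/0.901 = 150.
- Power of 90% or 95% with 10% overall dropout: about 207 or 256 (Lakatos-type).
- The Trial status calendar, taken as about 38 months of recruitment plus 4 months: event probability 0.921 and 0.835, mean 0.878; N = 130.2/0.878/0.9 = 165 to 135.4/0.878/0.9 = 171.

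**Effect of that calendar on 238.** Events = 238 × 0.9 × 0.878 = 188. Power is 92.0% (Schoenfeld) or 91.0% (Freedman).

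**The case against.** The strongest objection is that the paragraph never says the 10% is an overall figure. One choice of unit returns exactly the stated number with every other input as printed. On that view nothing is miscalculated; a unit has been left out. This stands in part. A reader might infer that 238 cannot be derived from the stated inputs at all, or that the power simply is 94%. Neither follows: the software output is not shown, and the monthly reading makes N and power consistent. What does not stand is that this leaves the paragraph sound. A dropout rate of 10% with no unit will be read as one patient in ten, and the reading that fits loses more than four in ten before progression.

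A second objection is that overpowering does no harm to validity. That is true: type I error is unaffected, and no interim analysis depends on N. The harm is a misdescribed basis for the trial's size.

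Third, a reader might infer that the Discussion's remark that "the sample size is relatively small, and this is due to limitations in staffing and funding" is contradicted by the high power. It is not. The remark concerns resources and makes no claim about power, so it needs no correction.

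**Conclusion.** The point holds in this form: the dropout rate, the power and N cannot all stand on the ordinary reading of the paragraph. With 10% lost overall, 80% power needs about 130 to 136 events and 152 to 158 patients, and 238 gives about 204 events and 93-94% power. The 238 is recovered only with 10% loss per month in each arm, about 132 events and about 44% lost before an event.

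The mismatch is certain; which figure was intended is not. A reader might conclude that heavy loss was forecast, but a unit slip in the software entry would produce the same 238, and the document does not distinguish the two. The figures assume exponential PFS, uniform recruitment and 15 months after the last enrolment. On the Trial status calendar the event count falls to about 188 and power to 91-92%, which still does not explain 238.

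**What to change.** Keep 238. In the Sample size section, state the time unit of the dropout rate and the number of PFS events required (about 130 to 136 for 80% power). Then correct whichever figure is wrong:

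- If 10% is overall, restate the power as about 93-94%, with about 204 expected events on 26 + 15 months.
- If 10% per month was intended, say so, disclose that about 44% of patients would be lost before a PFS event, and justify the assumption.

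Before printing an expected event count, reconcile the 26 + 15 months with the calendar under Trial status. If that calendar governs and dropout is 10% overall, the figures become about 188 events and 91-92% power. The Discussion needs no change. The cost is a few sentences in one section and a check of the software input, with no extra patients.

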### Statistical analysis

The primary analysis will be based on the intent-to-treat (ITT) principle (i.e. all patients will be analyzed according to their allocated treatment group). Missing primary endpoint data will be imputed conservatively. We will consider a sensitivity analysis using complete case, i.e. not imputing missing values, to assess if there is a difference in results. No interim analysis will be performed.

A statistician will perform the statistical analyses using SPSS 22.0 software (IBM, Armonk, NY, USA). Continuous variables will be summarized as the mean, standard deviation, median, minimum, and maximum. Means and standard deviations will be reported if the variable is normally distributed; if the data are skewed, medians and interquartile ranges will be used. Categorical variables will be expressed as numbers and percentages.

The baseline data will be summarized accordingly, depending on the data type (continuous, categorical). Categorical variables will be compared between groups using Pearson’s chi-square test. Continuous variables will be compared between groups using the two-sample *t* test (normally distributed data) or Mann-Whitney U test (non-normally distributed data). All statistical analyses will be performed based on a two-sided test. A *P* value ≤0.05 will be considered statistically significant, and the 95% CI will be calculated.

Survival data (PFS and OS) will be estimated using the Kaplan-Meier method. Differences between grouped survival profiles will be assessed by the log-rank test. Factors influencing survival (i.e., age, tumor, node, metastasis (TNM) staging, tumor differentiation status, lymph node metastasis, and chemotherapy cycles) will be analyzed using Cox proportional hazard regression analysis. Results will be expressed as HRs and 95% CIs.

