### Assessment

#### Baseline evaluations (conducted within 2 weeks of the start of protocol therapy)

We will collect baseline data as follows:Demographic dataAmerican Joint Committee on Cancer tumor diagnosis and stagingRelevant clinical disease history (diagnosis and treatment)Concomitant medicationPhysical examinationVital signsECOG-PS scoreImaging (computed tomography (CT) or magnetic resonance imaging (MRI))ElectrocardiogramLaboratory tests: routine blood test, liver and kidney functional electrolytes (including K^+^, Na^+^, Cl^−^, Ca^2+^, Mg^2+^)Tumor markers: CA153, carcinoembryonic antigen (CEA)Pregnancy test (if necessary)The European Organization for Research and Treatment of Cancer Quality of Life Questionnaire Core-30 (EORTC QLQ-C30, version 3)

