#### Other measures

Other measures will be performed as follows:Quality of life will be assessed using the EORTC QLQ-C30 version 3.0 [33]. The scores will be averaged and transformed linearly to obtain a range of scores, from 0 to 100, with higher scores indicating better quality of life.General health status is assessed using the ECOG-PS scale [34]. The scale divides the patient’s activity status into 0–5 levels. A higher level indicates a worse physical status.Laboratory examination: (1) hematology assessments: hemoglobin, white blood cell count, neutrophil count, and platelet count; (2) blood biochemical tests: total bilirubin, ALT, AST, alkaline phosphatase, serum creatinine, total protein, Na^+^, K^+^, Mg^2+^, Cl^−^, Ca^2+^, urea, and pregnancy test (if applicable); and (3) tumor marker detection: CA153 and CEA.

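### If the unadjusted two-sample tests are meant for follow-up QLQ-C30 scores, the comparison is valid but less precise than the collected baseline scores allow

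*Protocol article*

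**What the plan says.** The questionnaire is part of the baseline data set: "Quality of Life Questionnaire Core-30 (EORTC QLQ-C30, version 3" is listed under Baseline evaluations. The During treatment and Follow up sections repeat it every 6 weeks on treatment and once more 4 weeks after discontinuation.

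The Other measures section names it as an outcome, outside the primary and secondary lists: "Quality of life will be assessed using the EORTC QLQ-C30 version 3.0". Scores run from 0 to 100, so they are continuous.

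The relevant paragraph of the Statistical analysis section begins with baseline data: "The baseline data will be summarized accordingly, depending on the data type (continuous, categorical". It then assigns Pearson's chi-square test to categorical variables. For the rest it says "Continuous variables will be compared between groups using the two-sample" t test, or the Mann-Whitney U test when normality fails. The next sentence is general: "All statistical analyses will be performed based on a two-sided test".

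The only regression in the section concerns survival, where prognostic factors "will be analyzed using Cox proportional hazard regression analysis". No model is named for quality of life, and the text does not say whether follow-up scores or changes from baseline would be compared.

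**The concern.** When an outcome is measured before treatment on the same scale, the baseline score usually explains part of the spread in the follow-up score. A two-sample test on follow-up scores leaves that part in the error term. The confidence interval is then wider than it need be, and a chance baseline difference between arms is carried in part into the follow-up comparison.

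What is at stake is the precision of the patient-reported comparison of adding apatinib to vinorelbine. The validity of the trial and the primary endpoint are not in question.

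**Working it through.** **Step 1: does the test sentence reach the follow-up scores?** Two readings are possible.

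- Baseline only: the paragraph opens with the summary of baseline data, and the tests follow by data type.
- General: the test sentences carry no baseline qualifier, and the sentence after them speaks of all analyses. The companion chi-square sentence is also the only test in the article that could apply to objective response rate, disease control rate and grade 3 and 4 adverse events. On a baseline-only reading, these secondary outcomes would have no stated comparison.

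The general reading is the more plausible one, but the text does not settle it.

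**Step 2: inputs.**

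- Patients per arm: 119, or 119 × 0.9 = 107 after the 10% dropout (Sample size section). This number was set for PFS and is used here only as a head count.
- Two-sided alpha: 0.05, from the same section.
- Standard deviation, effect size and power for quality of life: none stated, so there is no figure of the plan to reproduce. The reference point is the difference that the unadjusted t test detects with 80% power.
- Baseline-to-follow-up correlation rho: not stated. It is assumed to be 0.3, 0.5 or 0.7.

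**Step 3: reference difference.** The noncentrality for 80% power is 1.96 + 0.84 = 2.80. In SD units the difference is d = 2.80 × sqrt(2/n):

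- n = 119: d = 2.80 × sqrt(2/119) = 0.363 SD
- n = 107: d = 2.80 × sqrt(2/107) = 0.383 SD

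**Step 4: effect of adjustment.** ANCOVA multiplies the residual variance by (1 − rho²). At the reference difference:

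power = Phi(2.80 / sqrt(1 − rho²) − 1.96)

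A t test on change scores multiplies the variance by 2(1 − rho), assuming equal SDs at both times:

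power = Phi(2.80 / sqrt(2(1 − rho)) − 1.96)

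| Assumed rho | Variance cut by ANCOVA | Power, follow-up scores | Power, change scores | Power, ANCOVA | n per arm for 80% power with ANCOVA |
|---|---|---|---|---|---|
| 0.3 | 9% | 80% | 65.8% | 83.6% | 109 |
| 0.5 | 25% | 80% | 80.0% | 89.9% | 90 |
| 0.7 | 49% | 80% | 95.1% | 97.5% | 61 |

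The last column is 119 × (1 − rho²), rounded up. The powers are the same at 107 per arm, because the reference difference is rescaled to keep the unadjusted test at 80%.

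**Step 5: chance imbalance.** A baseline difference carries over to follow-up in proportion to the baseline-to-follow-up slope. With equal SDs the slope equals rho, so at rho = 0.5 about half of the imbalance is expected to appear in the unadjusted comparison.

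**The case against.** A reader might infer that the plan fixes an unadjusted analysis of quality of life and throws the baseline score away. The documents do not support that, for two reasons. The test sentence names no outcome and may describe the baseline table only. A t test on changes from baseline is also a two-sample t test on a continuous variable, and it does use the baseline. Both objections stand, which is why the point is conditional. Change scores do not remove it, because they are no more efficient than ANCOVA: the table shows lower power at each assumed rho, and below rho = 0.5 they do worse than the raw follow-up scores.

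A second objection is that the article condenses a protocol not shown here, and that the quality-of-life model may be specified there or in an analysis plan. This stands as far as silence goes. But the section is not silent: it names the tests for continuous variables, and an analysis plan that followed it on the general reading would inherit the less precise method.

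Third, the gain depends on the reference point. For a true difference of 0.5 SD at 119 per arm, the noncentrality is 0.5 / sqrt(2/119) = 3.86, and unadjusted power is Phi(3.86 − 1.96), about 97%. Adjustment could then add no more than about 3 points of power. This is correct. The reduction in variance, and so the narrower interval, remains whatever the true difference.

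Fourth, a reader might infer that chance imbalance biases the result or passes into it in full. It does neither. Randomisation keeps the unadjusted comparison valid, and the carry-over in a given trial is only partial.

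**Conclusion.** The point holds in conditional form and is minor. If follow-up QLQ-C30 scores are compared by the stated two-sample tests, the comparison is valid but less precise than the data allow. At a design point of 80% power, the loss against ANCOVA is about 4 to 18 percentage points for assumed rho between 0.3 and 0.7. This rests on the general reading of the test sentence, on follow-up scores rather than changes being compared, and on a correlation that the documents do not give.

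Quality of life is neither a primary nor a secondary outcome, and no power is claimed for it. The PFS conclusion is unaffected.

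**What to change.** In the Statistical analysis section:

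1. Keep the t test and Mann-Whitney sentence for baseline description and for continuous measures that have no baseline value. Say so explicitly, which also removes the ambiguity of scope.
2. Add that QLQ-C30 scores are compared between arms by ANCOVA on the baseline score at a pre-specified visit. The alternative is a mixed model over the 6-weekly visits with baseline score, arm, visit and arm-by-visit interaction. Report the adjusted difference with its 95% CI.
3. State that the same approach may be used for other continuous follow-up measures with a baseline value, such as laboratory values and tumour markers, so that none is left without a method.

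The cost is a few sentences and a little more analysis work. The baseline scores are already collected, the named software (SPSS 22.0) fits both models, and nothing changes for patients.

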#### Inclusion criteria

The inclusion criteria are:Female patients with recurrent or metastatic TNBC, confirmed by histological or cytological examination.Age ≥ 18 years.At least one extracranial measurable site of disease according to Response Evaluation Criteria In Solid Tumors (RECIST) version 1.1 criteria [30] and an Eastern Cooperative Oncology Group performance status (ECOG-PS) score of 0–2.Expected survival ≥ 12 weeks.Negative for ER/PR: where ER < 1% indicates positive and PR < 1% indicates positive. Negative for HER-2 refers to: immunohistochemical analysis (IHC)1+ indicates HER-2 negative, IHC2+ indicates an uncertain case of HER-2, according to specific diagnostic criteria (the *Breast cancer HER-2 detection guide, 2014 edition*) [31]. Further, the in-situ hybridization (ISH) method will be used to detect HER-2 gene amplification for further diagnosis.All patients will be tested for bone marrow capacity, liver, and renal function within 7 days prior to enrollment, and will meet the following criteria:Routine blood test: absolute neutrophil (ANC) count ≥ 1.5 × 10^9^/L; hemoglobin ≥ 9.0 g/dL; platelet count ≥ 80 × 10^9^/L;Liver function: total bilirubin ≤ 1.5 times the upper limit of normal (ULN); alanine aminotransferase (ALT) and aspartate aminotransferase (AST) ≤ 2.5 × ULN (patients with liver metastasis ≤ 5 × ULN); alkaline phosphatase ≤ 4 × ULN;Renal function: serum creatinine ≤ 1.5 × ULN.Previous use of anthracyclines and/or taxanes.The medication history of vinorelbine meets one of the following conditions:No history of, or irregular vinorelbine use (the standard use of vinorelbine is defined based on the appropriate use of the medication as prescribed, for at least two cycles);Patients with advanced breast cancer, who receive a standardized regimen of vinorelbine for 6 months and have no cancer progression; they also have not used vinorelbine within 6 months prior to the first administration.Female patients of childbearing age must take adequate contraceptio, otherwise they must be proven to be infertile, that is:Patients over the age of 50 years are confirmed to have menstruation-deficient menopause for at least 12 months after stopping all exogenous hormone treatments;Under the age of 50 years; on this basis, it is also necessary to prove that the levels of progesterone and follicle stimulating hormone are in the postmenopausal range of the research institution;Women undergoing irreversible sterilization operations (hysterectomy, bilateral oophorectomy, bilateral salpingectomy, etc.) are negative for pregnancy and are not lactating before administration.No history of serious heart, lung, liver, or kidney diseases.Provision of written informed consent.

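### Baseline ECOG (0–2) is collected but enters no stated efficacy analysis: the unadjusted log-rank test for PFS and OS is valid, but it forgoes some power and leaves no planned answer to a chance imbalance

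*Protocol article*

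**What the plan says.** Protocol article, Statistical analysis: for PFS and OS, "Differences between grouped survival profiles will be assessed by the log-rank test". No strata or covariates are named. The Sample size section assumes the same plain log-rank test, and the Randomization section states no stratification factor.

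The Cox regression is directed at prognosis: "Factors influencing survival (i.e., age, tumor, node, metastasis (TNM) staging, tumor differentiation status, lymph node metastasis, and chemotherapy cycles". The list is closed by its i.e., and ECOG is not on it. The text does not say whether treatment is in this model, or whether TNM is taken at diagnosis or at study entry.

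Inclusion criteria admit an "Eastern Cooperative Oncology Group performance status (ECOG-PS) score of 0–2". ECOG is then recorded at baseline and every 6 weeks on treatment, and it appears under Other measures.

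**The concern.** The trial admits three levels of performance status, measures them before treatment, and then does not use them in the treatment comparison. If ECOG predicts PFS, three things follow. An unadjusted proportional-hazards estimate is pulled towards 1. The unadjusted test has less power than one that compares patients within ECOG level. And because no stratified randomization is stated, a chance ECOG imbalance between arms would be met by no planned adjusted analysis, so any later adjustment would look data-driven.

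This is more than detail left to an analysis plan that is not shown: the article names the test and closes the covariate list. A separate and smaller point is that lymph node status is the N of TNM, so the prognostic model lists overlapping factors while leaving ECOG out.

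**Working it through.** **Inputs from the Sample size section.** "power of 80%, and two-sided significance of α = 0.05"; "the mPFS was estimated to be 4.1 months in the vinorelbine monotherapy group and 6.7 months in the vinorelbine plus apatinib group"; from these medians the plan takes a ratio of 0.61 (4.1/6.7 = 0.612); "The recruitment time is expected to be 26 months"; "a 15-month follow-up time is planned"; 10% dropout with no time unit; 238 patients, 119 per arm.

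**Reproducing 238.**
- Schoenfeld events: 4 × (1.960 + 0.842)² / (ln 0.612)² = about 131.
- With 26 months of uniform accrual, 15 months of follow-up and no loss, the average event probability is 0.954. Then 131/0.954 = 138 patients, and 138/0.9 = 154. Freedman's 136 events give 143, then 159. So 10% lost overall does not give 238.
- The Lachin–Foulkes formula with a loss hazard of 0.10 per month gives 238.3, so 238 reproduces under that reading.

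Both readings of dropout are carried below, because they set the baseline power: about 95% and about 80%.

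**Which HR to hold fixed.** Take exponential PFS within each ECOG level k, with proportion p_k, control hazard λ_k and a common treatment HR h. The apatinib-arm curve is Σ p_k exp(−λ_k h t), which is the control curve read at time ht. Its median is therefore the control median divided by h: 4.1/0.612 = 6.7 months, whatever the ECOG effect. Under this model the plan's two medians correspond to a within-level HR of 0.612.

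**Simulation 1.** N = 238, control median 4.1 months. Assumed ECOG 0/1/2 mix 30/50/20%; assumed prognostic HR per ECOG level as shown. Power at two-sided 0.05, unadjusted versus ECOG-stratified log-rank:

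| HR per ECOG level | 10% lost overall | 10% lost per month |
|---|---|---|
| 1.3 | 94 vs 94% | 81 vs 80% |
| 1.6 | 91 vs 94% | 76 vs 78% |
| 2.0 | 87 vs 94% | 72 vs 78% |

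**Simulation 2.** Assumed mix 35/50/15%, 10% monthly loss, 4,000 trials per row:

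| ECOG HRs (0/1/2) | Unadjusted | Stratified log-rank | Adjusted Cox | Unadjusted HR |
|---|---|---|---|---|
| 1/1/1 | 79.5% | 78.0% | 79.0% | 0.61 |
| 1/1.2/1.5 | 78.6% | 77.8% | 78.9% | 0.61 |
| 1/1.4/2.0 | 76.7% | 77.4% | 78.5% | 0.62 |
| 1/1.5/2.5 | 76.3% | 78.6% | 79.8% | 0.62 |
| 1/2/3.5 | 71.8% | 78.0% | 79.1% | 0.64 |

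The adjusted HR stays at about 0.61 throughout. With no loss at all, 1/2/3.5 gives 89% against 94–95%, and an unadjusted HR of 0.65. The standard error of a power near 80% from 4,000 trials is √(0.8 × 0.2/4000) = 0.6 points, so differences of about a point are noise.

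**Hand check.** With 131 events, power is about Φ(½√131 × |ln HR| − 1.96). HR 0.612 gives Φ(0.85) = 80%, 0.62 gives Φ(0.78) = 78%, and 0.64 gives Φ(0.59) = 72%. The attenuated HR accounts for the loss.

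**Type I error.** With a true HR of 1 and ECOG HRs of 1/1.5/2.5, the unadjusted log-rank test rejects in 4.8% of trials.

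**Chance imbalance.** With the 30/50/20% mix the mean ECOG is 0.5 + 2 × 0.2 = 0.9 and the variance is 0.5 + 4 × 0.2 − 0.81 = 0.49. The SD of the between-arm difference in means is √(0.49 × 2/119) = 0.09 levels. About one trial in six is worse than that against apatinib. In those trials unadjusted versus stratified power is 90 vs 94%, 85 vs 95% and 70 vs 94% (10% lost overall), or 74 vs 80%, 66 vs 76% and 53 vs 81% (10% monthly), at 1.3, 1.6 and 2.0 per level. Each figure rests on only about 4,000/6 = 670 trials, so it can be off by 3 to 4 points.

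**The case against.** The strongest reply is that nothing here is wrong. An unadjusted log-rank test is a legitimate primary test and matches both the sample-size calculation and a randomization with no stated strata. Chance imbalance in ECOG is already covered by its 5% error rate. The documents give no ECOG distribution and do not say that ECOG predicts PFS, so any loss is conditional on assumptions, and the plausible range includes no loss. All of this stands. It limits the point to efficiency and prespecification.

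One defence does not stand: that the planning HR comes from overall medians and so protects the planned power. Under the exponential model used above, the two medians hold exactly whatever the ECOG effect, and the unadjusted test still loses power.

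A reader might also infer more than the documents support:
- That ECOG enters no analysis at all. It falls under the baseline summaries and between-arm comparison, and under Other measures. It is absent from the stated efficacy analyses.
- That TNM stage hardly varies. Recurrent as well as metastatic disease is eligible, and the time point of TNM is not given.
- That the overlap of TNM and nodal status weakens the primary result. It concerns only the prognostic Cox model.
- That prior treatment is ignored and vinorelbine exposure should be a stratum. The listed chemotherapy cycles may mean prior treatment, and no gain from stratifying by vinorelbine history has been shown.

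**Conclusion.** The point holds as a worthwhile improvement to a valid plan. Against an ECOG-stratified test, omitting ECOG costs about 0 to 3 points of power for a weak to moderate ECOG effect, and about 5 to 8 points for a strong one (HR about 2 per level). The estimated HR moves from 0.61 to at most about 0.65. Type I error is unaffected.

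These figures assume exponential PFS within level, a within-level HR of 0.612 and the ECOG mixes and prognostic HRs stated above, none of which except the medians comes from the documents. The size of the loss is similar under both readings of dropout. The case for acting does not depend on the average loss alone: a planned adjusted analysis is also the only clean answer to an unlucky ECOG split. It would be wrong to conclude that the primary test is invalid or that the trial is underpowered on this account.

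**What to change.** Before unblinding, amend the Statistical analysis section as follows.

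1. Test PFS and OS with a log-rank test stratified by baseline ECOG (0, 1, 2). State now the rule, such as a minimum number of events per level, by which levels collapse to 0–1 versus 2.
2. Report the treatment HR and 95% CI from a Cox model of treatment, stratified by or adjusted for baseline ECOG under the same rule.
3. Keep the unstratified log-rank test as a sensitivity analysis.
4. Separately, in the prognostic Cox model, add baseline ECOG, keep either TNM stage or lymph node status, and state when the retained factor is assessed. This does not touch the primary test.

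The cost is wording. ECOG is already collected, and stratified analysis does not require stratified randomization. The downside is a small efficiency loss if ECOG is not prognostic (79.5% to 78.0% for the stratified log-rank and to 79.0% for the adjusted Cox model in Simulation 2), and possible collapsing of a sparse level.
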